### Secondary outcomes

The following will be evaluated as secondary outcomes: (i) virological response rates (SVR 12 weeks post HCV antiviral therapy) will be compared between treatment groups; (ii) the change in APRI measurements from baseline to start of HCV treatment, to the end of HCV treatment (week 24) and 24 weeks post HCV treatment (week 48) will be compared between treatment groups; (iii) changes in glucose metabolism (HOMA-IR, fasting insulin, glucose levels) from baseline to 4, 8, 12, 24, 36 and 48 weeks; (iv) changes in lipid levels [total cholesterol, low-density lipoprotein cholesterol (LDL-c), high-density lipoprotein cholesterol (HDL-c), triglycerides] from baseline to 0, 12, and 36 and 48 weeks; (v) changes in anthropometric measures (waist circumference, body weight and BMI) from baseline to 0, 4, 8, 12, 24, 36 and 48 weeks; (vi) changes in liver-related inflammatory markers by (IL-6, IL-8, TNF-α, TGF-β, C-reactive protein (CRP)) from baseline to 0, 4, 8, 12, 24 and 36 weeks; (vii) changes in AFP levels from baseline to 0, 12, 24, 36 and 48 weeks; (viii) participant acceptability to study medication dosing will be assessed (in arm 1 only) at weeks 8, 24, and 48 weeks by questionnaire. Changes in scores from week 8 to end of study will be evaluated; (ix) changes in diet and physical exercise parameters from baseline to 24 and 48 weeks using dietary and physical activity questionnaires (Table 1).

### Safety assessments

Metformin has been studied in both HCV and HIV mono-infected patients with no increase in adverse events (AE) [18, 34]. Metformin does have the potential risk of lactic acidosis. A reduced dose (50 % of maximal dose) is used for patients with a CrCl < 60 mL/min. It is not recommended for use in patients with a creatinine clearance of < 30 mL/min. Patients will be cautioned against excessive alcohol intake, either acute or chronic when taking metformin, since alcohol intake potentiates the effect of metformin on lactate metabolism [35, 36].

A Data and Safety Monitoring Committee (DSMC) will be implemented to safeguard participant safety. All members will be independent from the study investigators. This committee will conduct regularly scheduled meetings to review the study progress including recruitment and conduct, and will identify any potential safety signals in the study population.

At each contact with the participant, information regarding adverse events (AEs) will be elicited by appropriate questioning and examinations. Any AE that occurs between the time that the participant is randomized and the time that s/he departs the study at the end of the final follow-up visit (or at the time of early withdrawal of the participant from the study for any reason) is to be recorded. Participants will also be monitored during the 48-week study period for serious adverse events (SAEs). If an SAE is ongoing at the time a participant discontinues/completes the trial, the SAE will be followed until the investigator agrees that the event is satisfactorily resolved, becomes chronic, or that no further follow-up is required (Table 1). 

### Study treatment adherence

The following criteria will be used to define compliance during this study:Adherence with study treatment will be assessed based on participant-provided information and tablet count, i.e., drug accountability, during follow-up visits. Non-adherence will be considered for participants who have an average daily intake of less than 80 % of their maximum tolerated dose.Attend baseline visit and all follow-up visits.Adherence with HIV antiretroviral therapy (ART) (if applicable) and HCV antiviral therapy will be documented as standard of care.

### Sample size calculation

To date there have been no studies that have investigated the benefits of improved IR in the HIV-HCV co-infected population or in HCV mono-infected patients. Studies that have investigated the effects of HCV antiviral therapy on FibroScan® score reported a 32 % reduction in mean score (10.6 +/- 4.8 kPa) compared with baseline in patients that obtained a treatment response [37]. Based on these study results, a sample size of 24 participants in each group would provide approximately 80 % power to detect a 4 kPa difference between the two treatment arms assuming a similar standard deviation. We anticipate a 20 % loss to follow-up, so an additional six participants will be randomized per group to account for loss to follow-up and to allow secondary outcome analyses. Using regression of the final measurement on the initial measurement will likely improve the power relative to using simple difference scores.

All analyses will be based on intention-to-treat basis and per protocol analysis. Intention-to-treat population will be defined as the set of all patients randomized.

### Statistical analysis

As the primary outcome of this study, the influence of metformin on preventing and promoting regression of liver fibrosis in HCV antiviral treatment recipients will be assessed by transient elastography. The change in transient elastography scores (kPa) at week 48 (24 weeks post HCV therapy) between groups will be assessed using linear regression adjusted for baseline score. We will also compare the trend on fibrosis progression over the course of the study (12, 24, 36 and 48 weeks) between groups using mixed-effects regression analysis. All analyses will be based on intention-to-treat basis. A sensitivity analysis of the change at 48 weeks will be conducted using multiple imputations to include those participants who do not have 48-week follow-up scores.

The same set of analyses based on a per protocol basis will also be performed. For the analysis, which examines the outcome longitudinally, participants who terminated the assigned treatment prematurely will be censored at the time that they went off treatment.

Secondary outcome measures include: virological response rates, changes from baseline to week 48 in indirect measures of liver fibrosis (APRI), inflammatory markers, metabolic measures, anthropometric measurements, HCV and HIV viral loads, AFP levels and liver function. Linear regression adjusted for baseline score will be used to compare the outcome at week 48 between groups. Mixed-effects regression analysis will also be used to compare the trend over time between groups.

To account for potential confounding factors (i.e., HCV/HIV viral status, alcohol consumption, IR, BMI) associated with changes in liver fibrosis, a sensitivity analysis based on multivariate regression analysis will be performed.

Patient acceptability of daily long-term study treatment use will be evaluated (in arm 1 only) using the Treatment Satisfaction Questionnaire for Medication. Patient acceptability will be assessed based on change in median score from week 8 (first administration of questionnaire) to week 24 and week 48. Descriptive statistics will be used to summarize the data.

Baseline characteristics will be expressed as mean and standard deviation (SD) for continuous variables and percentages for categorical variables. Baseline variables to be considered include: age, gender, ethnicity, HCV genotype and viral load, HIV viral load and CD4 count (as per SOC), HbA1c, HOMA-IR, FibroScan® scores, smoking history, alcohol consumption, and illicit drug use.

Lifestyle modification will be evaluated through changes in physical activity (changes in median MET/week, percentage change in participants classified as low, medium and high level of activity) and dietary changes (change in median daily caloric intake, daily consumption of fat, protein, carbohydrates and micro/macro nutrients). Linear regression adjusted for baseline score will be used to compare the outcome at week 48 between groups. Mixed-effects regression analysis will also be used to compare the trend over time between groups.

Data will be collected on liver-related complications (progression of liver fibrosis stage, HCC, transplantation) and mortality. We anticipate that the event rate will be low given the small sample size and short duration of follow-up.

Subgroup analyses will be conducted based on SVR to compare the effect virological response influences liver fibrosis and the benefit of metformin in reducing progression of fibrosis. Subgroup analyses will also be conducted based on HIV status to compare the influence of HIV infection on progression of liver fibrosis and benefit of metformin in reducing the progression of fibrosis.

Subgroup analyses based on metformin doses (full dose versus not) in the metformin group and weight loss in patients in both treatment arms will also be conducted. These additional analyses will be useful in determining if lower doses can achieve the same benefit and the impact that potential weight loss associated with this medication may have on steatosis and improving liver outcomes respectively.

Subgroup analyses will also be conducted based on end of study HOMA-IR score (<2 vs. > 2) to evaluate if the benefits of metformin are dependent or independent of the insulin-sensitizing effects of this treatment.

As a sensitivity analysis, we will also consider using multiple imputation techniques to impute missing data for the primary outcome at 48 weeks. Linear regression adjusted for baseline score will then be used to compare the groups.

When half (n = 30) of the participants have completed their 48-week visit, an interim analysis of efficacy will be conducted. The same technique and analytic strategy will be used to analyze the primary end point, transient elastography score (kPa) at 48 weeks. An intention-to-treat approach will be taken, linear regression adjusting for baseline score, and missing imputations to account for missing data will be used. The O’Brien-Fleming approach using the Lan-DeMets alpha spending function will be used, so that the criterion for statistical significance at the first analysis will be 0.005 and the criterion at the final analysis will be 0.048 to maintain 80 % power overall. This analysis will be supplemented by a mixed-effects regression model examining the outcome at all time points for all patients available, and adjusting for baseline values.

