### Study design and setting

This study is a prospective 48-week single-centre, randomized, open-label, controlled trial of HIV-HCV co-infected and HCV mono-infected patients with IR (HOMA-IR ≥ 2.0) who are planning to initiate HCV antiviral therapy.

Sixty (60) participants meeting eligibility criteria will be randomized in a 1:1 ratio using variable block sizes to either arm 1, metformin 2 g [1 g twice a day (BID)] plus lifestyle, or to arm 2, lifestyle alone (the control arm). Randomization will be stratified according to HIV status and according to stage of liver fibrosis (F0–2 vs. F3–4) and will be conducted utilizing a web-based randomization system. The allocations will be generated by a statistician unassociated with the study using the SAS statistical program (SAS Institute, Inc., Cary, NC, USA) and uploaded into the randomization system. A log of all transactions including date and time of randomization, stratum and treatment allocation will be recorded. The randomization system will be accessed by the study coordinator at the study site when they have identified consenting eligible participants ready to be randomized.

Arm 1 (Metformin group) will receive metformin and lifestyle treatment during a 12-week period prior to starting HCV therapy (week 0–12), during the 12-week treatment phase (week 12–24) and 24 weeks post HCV treatment (week 24–48). Participants who require > 12 weeks of HCV treatment will be excluded. If initiation of HCV treatment is delayed beyond 12 weeks, participants will continue on metformin during this time period and will receive less metformin post HCV treatment. Arm 2 (Control group) will receive lifestyle treatment alone during a 12-week period prior to starting HCV therapy (week 0–12), during the 12-week treatment phase (week 12–24) and 24 weeks post HCV treatment (week 24–48). A detailed study flow chart is depicted in Fig. 1.

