### Selection of participants

Participants will be recruited from The Ottawa Hospital Viral Hepatitis Clinic. Study recruitment will begin in July 2016. All adult patients between the ages of 18 and 79 years of age, who have provided informed consent, have documented history of chronic HCV RNA infection with evidence of fibrosis on FibroScan® > 8.0 kilopascals (kPa) or liver biopsy score > 2 (Batts-Ludwig System [33] within 2 years, insulin resistance as determined by a HOMA-IR of > 2.0 at screening and intend to start an 8–12 week interferon (IFN)-free HCV antiviral therapy. If participants are HIV-infected and not on HIV antiviral therapy, they will require a CD4 count of at least 200 to be included in the study.

Individuals will be excluded from the study if they are: pregnant, suspected to be pregnant, planning to become pregnant or breastfeeding, have a chronic HBV infection, an HbA1c > 8.0 %, are using immune-suppressing medications, have an active malignancy, are currently or previously treated with metformin or other oral diabetes medications or insulin, have a history of pre-existing diabetes (type 1, type 2 or gestational diabetes), clinical evidence of decompensated cirrhosis (ascites, esophageal varices, hepatic encephalopathy, hepatocellular carcinoma), renal impairment [serum creatinine levels > = 136 umol/L (males), > = 124 umol/L (females)], history of congestive heart failure requiring pharmacologic therapy, Wilson’s disease, alpha-1 antitrypsin, hemochromatosis, biliary cirrhosis, alcohol consumption > 50 g/day on average, participation in other clinical investigations during the study, or a history of lactic acidosis irrespective of precipitating factors.

Active illicit drug use (IDU) and stable health illness will not be exclusionary assuming it is unlikely to compromise study adherence to protocol and study drug. In HIV-infected participants, HIV antiretroviral use and suppressed HIV viral load will not be required for participation.

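### The stated models adjust for the baseline score but not for the factors that stratify randomisation; if those factors, chiefly HIV status, are prognostic beyond baseline, the test is slightly conservative and a little power is lost

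*Protocol article*

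**What the plan says.** Protocol article, Study design and setting: "Randomization will be stratified according to HIV status and according to stage of liver fibrosis (F0–2 vs. F3–4"). Sixty participants are allocated 1:1 in variable blocks.

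Protocol article, Statistical analysis:

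- **Primary outcome.** The week-48 change in kPa "between groups will be assessed using linear regression adjusted for baseline score".
- **Interim analysis.** The same approach at half recruitment: "linear regression adjusting for baseline score, and missing imputations to account for missing data will be used".
- **Secondary, lifestyle and imputation analyses.** Each is again a linear regression on the baseline score. The mixed-effects models are given no covariates, except at the interim, where baseline values are named.
- **Sensitivity analysis.** A separate multivariable model, with this stated purpose: "To account for potential confounding factors (i.e., HCV/HIV viral status, alcohol consumption, IR, BMI) associated with changes in liver fibrosis". Fibrosis stage is not in that list.
- **Subgroups.** HIV status also has its own subgroup analysis.

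Neither stratification factor is named in the primary, interim or continuous secondary models.

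**The concern.** Stratified blocks force the arms to be nearly alike on HIV status and stage. Variation in outcome due to those factors then largely cancels out of the difference between arms, so the true sampling variance falls. A regression that omits the factors still counts that variation in its residual variance. The reported standard error is then larger than the true one, the confidence interval is too wide and the test rejects too rarely.

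The plan gives a reason to expect some such effect. It names HIV viral status among the factors associated with fibrosis change, and its sample size section expects regression on the initial measurement to help power. With 24 evaluable participants per arm, the power calculation has almost no margin. At stake is a modest amount of efficiency, not validity.

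**Working it through.** **Inputs**

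- Sample size calculation: difference 4 kPa, SD 4.8, 24 evaluable per arm, about 80 % power, 20 % loss, 30 per arm randomised.
- Statistical analysis: final criterion 0.048.
- Assumed, because the documents do not give them: a two-sided test; the correlation ρ between baseline and week-48 kPa; and R², the share of the variance left after baseline that the strata explain.

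**1. The plan's own figure.** The standard error is 4.8 × √(2/24) = 1.386, and 4/1.386 = 2.89. The noncentral t with 46 df gives power 80.7 % at 0.05 and 80.2 % at 0.048. Also 24/0.8 = 30. The plan's figure reproduces.

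**2. Standard error and size when the factors are omitted.** With perfect balance, the reported standard error exceeds the true one by a factor 1/√(1 − R²). The true size of a nominal 0.05 test is 2 × [1 − Φ(1.96/√(1 − R²))].

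| R² | SE ratio | True size |
|---|---|---|
| 0 | 1.00 | 0.050 |
| 0.05 | 1.03 | 0.044 |
| 0.10 | 1.05 | 0.039 |
| 0.15 | 1.08 | 0.034 |

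**3. Power at 0.048, 24 per arm.** The residual SD after baseline is s₀ = 4.8√(1 − ρ²), which is 4.80 at ρ = 0 and 4.16 at ρ = 0.5. The SD after the strata as well is s₁ = s₀√(1 − R²). Both models have noncentrality 4/(s₁√(2/24)). The model with the factors uses the ordinary t critical value on 43 df. The model without them has 45 df, and its critical value is in effect multiplied by 1/√(1 − R²).

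| ρ | R² | Baseline only | With both factors | Difference (points) |
|---|---|---|---|---|
| 0 | 0 | 80.1 % | 80.0 % | −0.1 |
| 0 | 0.05 | 80.7 % | 82.0 % | 1.3 |
| 0 | 0.10 | 81.3 % | 84.0 % | 2.7 |
| 0 | 0.15 | 82.0 % | 86.0 % | 4.1 |
| 0.5 | 0 | 90.0 % | 90.0 % | −0.1 |
| 0.5 | 0.05 | 90.6 % | 91.4 % | 0.8 |
| 0.5 | 0.10 | 91.1 % | 92.7 % | 1.6 |
| 0.5 | 0.15 | 91.7 % | 94.0 % | 2.3 |

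Differences are taken before rounding.

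**4. Simulation with imperfect balance.** Stratified blocks of 2 and 4, 60 randomised, 48 evaluable, 30 % HIV-positive (assumed), stage as dichotomised baseline kPa, nominal 0.048, 6,000 runs per scenario. Results at ρ = 0.5 with an effect of HIV status only:

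- R² = 0: mean model SE 1.203 against an empirical 1.212, type I error 0.046. Nothing is overstated. Adding the factors lowers power from 89.5 % to 88.9 %.
- R² = 0.10: SE 1.205 against 1.160 (about 4 % too large), type I error 0.040, power 90.1 % without and 91.5 % with the factors.
- R² = 0.20, beyond the range used above: SE 1.203 against 1.120 (about 7 % too large), type I error 0.031, power 91.0 % against 94.5 %.

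**5. Fibrosis stage separately.** A 2 kPa step effect of stage on top of the linear effect of baseline kPa gave power 89.3 % without and 89.2 % with the factors, so no gain. For a secondary outcome adjusted for its own baseline instead of kPa, stage is less redundant. With an assumed 5 % of residual variance from each factor, a similar simulation gave size 0.039 without and 0.050 with the factors, and power 81.4 % against 83.7 %.

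**The case against.** The strongest objection is that the loss depends on a condition the documents do not establish. They give no estimate of how far HIV status or stage predicts week-48 kPa once baseline kPa is known. At R² = 0 the omission costs nothing and the added covariates cost a little. This stands, and the point must be stated conditionally.

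Second, continuous baseline kPa measures the same construct as stage more finely. This largely stands for the kPa models. It is not complete: entry is by "evidence of fibrosis on FibroScan® > 8.0 kilopascals (kPa) or liver biopsy score > 2", and the article does not say whether FibroScan or biopsy assigns the stratum. A biopsy-based stage need not track baseline kPa. Nor does the objection reach HIV status or the secondary outcomes.

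Third, HIV is not ignored, since it enters a sensitivity model and a subgroup analysis. True, but neither changes the primary standard error.

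Fourth, the article is condensed and never says that baseline is the sole covariate. That is fair for the mixed-effects models, where covariates are mostly unstated. For the linear models it names the adjustment repeatedly, and that adjustment does not match the randomisation.

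A reader might go further and infer that the analysis is biased or anti-conservative, that the trial is underpowered, or that the benefit of stratifying is lost. The documents support none of these. The error is on the conservative side. The sample size used the unadjusted SD of 4.8, and baseline-only power in the table rises with R² and never falls below 80.1 %. Balance still reduces the true variance; only the reported standard error fails to reflect it.

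**Conclusion.** The mismatch between design and stated analysis is real and its consequence is conditional and small. If the strata explain 5 % to 15 % of the variance left after baseline (an assumed range), the reported standard error is about 3 % to 8 % too large and the true size of a nominal 0.05 test is 0.044 to 0.034. The power lost at 0.048 is about 1 to 4 points with no baseline correlation and about 1 to 2 points at a correlation of 0.5. These figures assume perfect balance and a two-sided test; the simulated losses at R² of 0.05 and 0.10 were somewhat smaller. At R² = 0 there is no loss. For the kPa outcome the concern is mainly HIV status, which the plan itself regards as related to fibrosis change. Validity and the planned 80 % power are unaffected. Severity: minor.

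**What to change.** Add HIV status (yes/no) and fibrosis stratum (F0–2 or F3–4, as randomised) as fixed covariates, next to the continuous baseline value. Apply this to the primary week-48 model, the interim model, the mixed-effects models and the continuous secondary models. Keep alcohol consumption, IR and BMI in the sensitivity analysis. State whether FibroScan or biopsy assigns the stratum.

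The cost is a line of text and two degrees of freedom: 45 to 43 residual df with 48 evaluable, and 27 to 25 at an interim of 30. If the factors turn out not to be prognostic, the price is about 0.1 power point analytically and under one point in simulation. In the kPa model the stage term may add almost nothing, but including it keeps the model in line with the randomisation. Fixing the covariates in advance also removes any later choice between an adjusted and a baseline-only result.

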The effect of DAA HCV treatments on insulin resistance and long-term risk of type 2 diabetes has yet to be clearly established. A randomized controlled trial of HCV mono-infected study participants receiving 14 days of monotherapy with the protease inhibitor danoprevir, found that serum HCV RNA and homeostatic model assessment of insulin resistance (HOMA-IR) correlated significantly (Spearman rho = 0.379, *p* < 0.0001) [16]. At the end of 14 days of danoprevir monotherapy the mean decrease in HCV RNA was 2.2 ± 1.3 log10 IU/ml (*p* < 0.0001) in patients who received the active drug (*n* = 40), which correlated with a decrease in mean HOMA-IR score by 1.6 ± 1.1 (*p* < 0.0001). In contrast, HCV-RNA and HOMA-IR remained unchanged in placebo recipients. The role of insulin resistance and hyperglycemia as predictors of SVR with DAA HCV treatment has not been clearly established. There are also no studies to date that have examined the role insulin resistance or hyperglycemia play in promoting progression or preventing regression of liver fibrosis in patients that have achieved SVR with HCV antiviral therapy.

In high-risk populations, metformin, an insulin sensitizer, has been shown to delay or prevent the onset of T2DM [17]. While it is unknown whether this specific benefit extends to those infected with HCV, metformin does improve HCV treatment and liver-related outcomes. At least one study showed treatment with metformin resulted in higher SVR rates when compared with the control group (59.2 % vs. 38.8 %, chi-square 4.083, *p* = 0.043) [18]. HCV-infected patients with cirrhosis and T2DM who were taking metformin had a decreased risk of developing HCC [19, 20].

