At the cellular level, metformin is highly concentrated in the liver and improves IR through the activation of AMP-activated protein kinase (AMPK) which decreases gluconeogenesis in the liver and increases glucose uptake in the skeletal muscle [21]. In vitro studies have demonstrated that pharmacologic activation of AMPK with metformin may have antifibrotic effects by inhibiting the transforming growth factor beta (TGF-β1)-induced fibrogenic property of HSCs via transcriptional coactivator p300 [22]. TGF-β1 is the most characterized of the fibrotic cytokines and has been found to be increased in HCV-HIV co-infected patients [23]. It has also been proposed that the anticancer effects of metformin in HCV-infected patients may also be via AMPK and the inhibition of mammalian target of rapamycin (mTOR), which in turn regulates cell cycle progression and cell growth [24]. There are no studies to date that have looked at the effect of metformin in preventing progression of liver fibrosis or accelerating regression fibrosis in patients treated with HCV antiviral therapy.

Alpha-fetoprotein (AFP) is an oncofetal protein associated with hepatic malignancies and liver regeneration [25, 26]. HCV core protein, inflammation, necrosis and hepatocellular injury have all been suggested as causes for elevated AFP levels in chronic HCV infection [25–28]. Although type 2 diabetes and insulin resistance have been identified as risk factors for the progression of liver fibrosis and development of hepatocellular carcinoma the mechanism by which this occurs is not clear [9, 11, 29, 30]. The relationship between AFP and insulin resistance was recently examined in a retrospective analysis of 300 HCV-infected patients [31]. This study demonstrated that whole-body insulin resistance and hepatic fibrosis correlated directly with elevated levels of AFP lifestyle modification over a 3-month period correlated with improved insulin resistance and a reduction in AFP levels. This study draws attention to the need for further prospective studies to understand the relationship between insulin resistance, AFP, hepatic fibrosis and hepatocarcinogenesis. No studies have examined the effect of metformin, an insulin sensitizer, on AFP levels.

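### HCV viral load is compared between arms at week 48, when cure leaves almost nothing to compare, and no contrast is named at the end of the antiviral-free phase

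*Protocol article*

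**What the plan says.** The Statistical analysis section of the protocol article lists the secondary measures as virological response and "changes from baseline to week 48 in indirect measures of liver fibrosis (APRI), inflammatory markers, metabolic measures, anthropometric measurements, HCV and HIV viral loads", followed by AFP and liver function. It then fixes the method: "Linear regression adjusted for baseline score will be used to compare the outcome at week 48 between groups". A second analysis follows: "Mixed-effects regression analysis will also be used to compare the trend over time between groups".

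The Study design and setting section divides the 48 weeks into three phases. Arm 1 "will receive metformin and lifestyle treatment during a 12-week period prior to starting HCV therapy (week 0–12"), then continues "during the 12-week treatment phase (week 12–24) and 24 weeks post HCV treatment (week 24–48"). Arm 2 follows the same calendar with lifestyle treatment alone. Antiviral treatment may start later than week 12.

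The Objectives section names HCV viral status, separately from SVR, among the measures on which metformin's effect is to be considered. The Secondary outcomes section includes "changes in glucose metabolism (HOMA-IR, fasting insulin, glucose levels) from baseline to 4, 8, 12, 24, 36 and 48 weeks". It lists AFP at week 12 and later, and inflammatory markers at weeks 4, 8, 12, 24 and 36. Table 1 samples HCV RNA, fasting insulin and glucose, and inflammatory markers at weeks 4, 8 and 12, and AFP at week 12.

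**The concern.** By week 48 both arms have had the same antiviral course. Every cured participant then has HCV RNA at the assay floor, whichever arm they are in. Change from baseline is therefore fixed by the baseline value, and any difference between arms comes from the few treatment failures. A regression on that outcome does not address whether metformin alters viral load.

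The design contains a phase that could address it. In weeks 0 to 12 the arms differ only by metformin on top of lifestyle treatment, with no antiviral. The samples are taken, but the plan names no between-arm contrast at the end of that phase for HCV RNA, HOMA-IR, insulin, glucose, AFP or inflammatory markers.

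The Background section gives reason to care about HOMA-IR and AFP as well. In a 14-day antiviral study HCV RNA fell, "which correlated with a decrease in mean HOMA-IR score by 1.6 ± 1.1". On AFP it says: "HCV core protein, inflammation, necrosis and hepatocellular injury have all been suggested as causes for elevated AFP levels in chronic HCV infection". If clearing the virus moves these markers, a contrast before antivirals separates metformin's contribution from that of cure more cleanly than one read afterwards.

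**Working it through.** **Plan's own figure.** The document gives no power or precision figure for these secondary outcomes. The nearest is the primary-outcome sample size: 24 per group, 4 kPa difference, SD 4.8 kPa, about 80 % power. With two-sided alpha 0.05 (sidedness is not stated), the normal formula gives 82.3 % and the noncentral t gives 80.7 %, so the figure is reproduced. It is used here only as the source of 2 × 24 = 48 evaluable participants.

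**HCV RNA at week 48.** Let p be the cure rate. The document gives none for direct-acting antivirals, so a range is assumed. The expected number still viraemic is 48 × (1 − p). The chance that a given arm of 24 has no viraemic participant is p^24.

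| Assumed cure rate | Expected viraemic of 48 | Chance that an arm of 24 has none |
|---|---|---|
| 85 % | 48 × 0.15 = 7.2 | 2 % |
| 90 % | 48 × 0.10 = 4.8 | 8 % |
| 95 % | 48 × 0.05 = 2.4 | 29 % |
| 98 % | 48 × 0.02 = 1.0 | 62 % |

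A linear regression with about 41 to 47 of 48 values at the floor is in effect a comparison of failure counts. The SVR outcome already makes that comparison.

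**What is named for weeks 0 to 12.** Setting the sections side by side:

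- Statistical analysis: one time-point test, at week 48, plus one trend comparison over the study.
- Secondary outcomes: changes to weeks 4, 8 and 12 for glucose metabolism and inflammatory markers, and to week 12 for AFP. HCV viral load is not a separate item there.
- Table 1: all of these, and HCV RNA, are sampled by week 12.

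The trend comparison uses the early values. It spans the pre-antiviral, on-treatment and post-treatment phases, so it does not isolate weeks 0 to 12.

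**HOMA-IR.** With 24 per arm, the difference detectable with 80 % power at two-sided 0.05 is (1.96 + 0.84) × √(2/24) = 0.81 SD, at week 12 or week 48. What matters is whether the true difference shrinks between them, and the document does not say.

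- If metformin's effect is additive, there is no shrinkage.
- If it is proportional, with reduction r from baseline B, the difference is rB before cure and r(B − 1.6) after it. This borrows the 1.6 from the 14-day study. The share lost is 1.6/B: 53 % at B = 3, 40 % at B = 4, 32 % at B = 5.
- Illustration, assuming a week-12 difference of 1.0 and SD 1.1 (borrowed from the same study) held constant: power is 87 %. If 75, 50 or 25 % of the difference remains at week 48, power is 64, 34 or 12 %. With SD 1.5 the four figures are 62, 40, 20 and 9 %.

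These figures show what would follow from shrinkage. They do not show that it occurs.

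**The case against.** The strongest reply is that most of this is already covered. The mixed-effects analysis uses every visit, and early changes in most of the markers are listed as secondary outcomes. For APRI, the change to the start of HCV treatment is explicitly to be compared between groups. Visit-specific contrasts within a stated mixed model are often left to a statistical analysis plan, which is not shown here. This stands in part: the early data are not discarded. But the article does fix week 48 as the one named time point, including for HCV viral load, where that choice defeats the purpose.

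A reader might infer that the week-48 comparisons of HOMA-IR, AFP and inflammatory markers are also invalid or biased. The document does not support that. Metformin continues to week 48, so the arms still differ in treatment, and a shift common to both arms does not bias their difference. Week 48 also matches the time of the primary regression. Week 12 has its own limit, since the metformin dose is stepped up over the first weeks and exposure is shorter.

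A reader might also take the 32 to 53 % loss for HOMA-IR as established. It rests on an assumed proportional effect, assumed baselines, and a figure from 14 days of a single drug that reduced HCV RNA but was not a cure. The Background section itself says the effect of these antivirals on insulin resistance is not settled. If cure scaled values down, the spread between participants could shrink too, and power need not fall. For inflammatory markers, movement with cure is inference.

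Nor is the mechanistic question left out altogether. HOMA-IR is an outcome at six visits and enters the trend model, and a subgroup analysis by end-of-study HOMA-IR is planned.

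**Conclusion.** The point holds firmly for HCV viral load. With cure assumed at 85 to 98 %, about 7 to 1 of 48 participants would be off the assay floor at week 48. The planned regression therefore largely duplicates the SVR comparison and cannot inform the stated objective on HCV viral status.

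For HOMA-IR, insulin, glucose, AFP and inflammatory markers it holds only as a gap: the antiviral-free phase is built into the design and sampled, but has no named contrast. Week 48 stays valid for these outcomes. It loses sensitivity only if cure shrinks the between-arm difference, by an amount the document does not give. Making week 12 the main analysis for every marker is therefore a trade-off, and the document does not require it.

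These are secondary outcomes in a pilot trial, and the primary analysis is not affected. The change is worth making because it is cheap.

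**What to change.** 1. Drop the week-48 linear regression of HCV RNA and report post-treatment RNA as SVR only.
2. Compare HCV RNA between arms, adjusted for baseline, at the last visit before the first antiviral dose. This is week 12 for participants who start on schedule. State how delayed starts are handled, so that no sample taken after the first dose counts as pre-antiviral.
3. Add the same pre-antiviral contrast for HOMA-IR, fasting insulin and glucose, AFP and inflammatory markers. The planned mixed model can supply it, with visit as a category and an arm-by-visit term. Keep week 48 as a second contrast, described as the effect of metformin in combination with antiviral treatment.
4. Reconcile the inflammatory-marker time points: Secondary outcomes stops at week 36, while Statistical analysis compares at week 48 and Table 1 samples at week 48.

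No visit, sample or participant is added. The cost is one more reported contrast per secondary outcome, which should be labelled as secondary.
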